## 4 Trial Design

### Study Endpoints

The primary endpoint is health-related quality of life measured 16-weeks following randomisation (i.e. end of the intervention period).

Secondary endpoint is health-related quality of life measured 12-months following randomisation.

### Study Design

A randomised controlled clinical trial will be conducted. Figure 1 illustrates the participant flow in the chart below.

*Figure 1: Participant flow chart in the SMART exercise program study*

[figure not shown]

### Bias

To reduce the bias, three strategies will be implemented. First, the personnel responsible for recruitment will be blinded to the randomisation (i.e. the randomisation sequence will be concealed). Second, to minimise contamination, separate groups of clinicians will carry out the SMART program and the usual care. Finally, assessors blinded to the group allocation will conduct all assessments following randomisation.

### Blinding and Randomisation

Participants will be randomised (ratio of 1:1) to the experimental or control group, with computer generated randomisation using REDcap software. The randomisation sequence will be stratified for, (i) treatment pathway (chemotherapy, hormonal treatment and/or surgery), (ii) whether the person lives in Perth or outside Perth (i.e. rural or remote location) and (iii) whether the person regularly engaged in

exercise (or not) prior to their BC diagnosis. The randomisation sequence will be concealed using the REDcap software.

Data collected during all re-assessments (i.e. following randomisation) will be performed by a researcher blinded to group allocation.

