Nevertheless, National and International organisations e.g., the Clinical Oncology Society of Australia (COSA) routinely recommend that following any cancer diagnosis, individuals should complete at least 150 minutes per week of moderate intensity aerobic exercise or 75 minutes per week of vigorous intensity aerobic exercise, as well as two resistance training sessions each week (COSA 2018, World Cancer Research Fund, 2018). Exercise during cancer treatments has been widely studied and reported as a safe intervention for individuals with cancer (Cormie 2018). However, despite the clear clinical guidelines and safety reports, approximately 80% of women with BC do not meet these exercise recommendations and 23% reduce their usual activity level during cancer treatment (Gildea 2023). Systematic reviews suggest that even if supervised exercise programs successfully increase physical activity levels, these physical activity levels were maintained in only four out of ten trials (Weemaes et al., 2023). Women with BC commonly report that transitioning from supervised to self-managed exercise is one of the most significant barriers to maintaining physical activity (Ferri et al., 2021). Hence, there is a clear need to develop strategies to improve adherence to participation in exercise in this population.

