### 3 Trial Aims / Objectives / Hypotheses

For all research questions, the study population refers to adults with newly diagnosed with breast cancer who are undergoing treatment through the Breast Clinic at RPH.

Primary research questions:

- 1) Does the SMART program, compared with usual care, change health-related quality of life (primary outcome) measured 16-weeks and 12-months following randomisation?
- 2) Does the SMART program, compared with usual care, change peripheral muscle strength, muscle mass, exercise tolerance, exercise adherence and chemotherapy completion rates (secondary outcomes) measured 16 weeks following randomisation?

Secondary research questions:

- 1) Do factors such as adherence, treatment pathway and cancer stage moderate the magnitude of any change in primary or secondary outcomes? (i.e. moderator analysis)
- 2) What is the health care utilisation, absenteeism and presenteeism over the 12 months following randomisation? (descriptive analyses only, to guide patient expectations in regarding these outcomes)

- 3) Does performance on tests of peripheral muscle force-generating capacity and exercise tolerance, change with test repetition (i.e. is there a learning effect)? (can be answered by Honours students enrolled in the BSc physiotherapy at Curtin University)
- 4) What is the minimal detectable difference in health-related quality of life and exercise tolerance? (can be answered by Honours students enrolled in the BSc physiotherapy at Curtin University)
- 5) Do psychological determinants of behavioural change, such as capability, opportunity, and motivation affect adherence to the SMART program and physical activity maintenance?
- 6) Does the SMART program improve mood, and does mood influence adherence to the program and physical activity maintenance?

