### Participant inclusion criteria

Adults will be eligible to participate if they meet the following criteria:

1. Adult with newly diagnosed breast cancer (within the last 6 months)
2. Consent to treatment for their BC, which may include chemotherapy and/or endocrine therapy

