## OTHER VARIABLES

**Descriptive variables** will be recorded such as age, sex, body mass index, employment status, co-morbid conditions, stage of cancer and details of cancer treatment.

**Healthcare utilisation and adherence with exercise** will be assessed in both groups. In the control group, this will be documented during the monthly phone calls and exercise diaries. In the experimental group, this will be monitored by asking each participant during the weekly supervised sessions and also using exercise diaries (see Section 4, Monitoring). Regarding healthcare utilisation, we will ask each participant to recall the number of; (i) visits to the Emergency Department, (ii) inpatient admission days, (ii) outpatient appointments and, (iii) visits to any other healthcare provider (Y/N, who, number of visits). Regarding adherence with exercise, we will ask each participant to recall the number of minutes spent engaging in moderate or vigorous intensity exercise and details regarding any resistance exercise.

**Absenteeism and presenteeism** will be assessed using the iMTA productivity cost questionnaire (Bouwman 2015).

**Global rating of change** will be assessed by asking participants, on completion of the SMART exercise program, to indicate if their health-related quality of life or exercise tolerance had 'improved', 'worsened' or 'stayed the same'. Those participants who rated their walking ability as 'improved' or 'worsened' will then be asked to rate the degree of change on a seven-point scale (1 a little better to 7 a great deal better).

**Feasibility and acceptability** will be measured using; (i) Quantitative data from an acceptability and feasibility questionnaire, and (ii) qualitative data from exit interviews. These are described below:

*Quantitative data* will be collected using a questionnaire asking participants to rate their perceptions of the SMART exercise program (e.g., "*I thought the SMART exercise program was easy to understand*"). Participants can rate each item on a five-point scale (1 "*I don't agree at all*" to 5 "*I totally agree*"). Four open-ended items at the end of this questionnaire allow participants to include additional feedback (e.g., "*What did you like about the SMART exercise program?*").

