| SRBAI                                                    | x                        |                                                | x                                             | x                                                 | x                                        |
| PANAS                                                    | x                        |                                                | x                                             | x                                                 | x                                        |
| Participation in exercise                                |                          | X                                              |                                               |                                                   |                                          |
| Healthcare utilisation                                   |                          | X                                              |                                               |                                                   |                                          |
| iMTA (absenteeism / presenteeism)                        |                          |                                                | X                                             | X                                                 | X                                        |
| Acceptability/ feasibility                               |                          |                                                |                                               | x                                                 |                                          |
| Exit interview                                           |                          |                                                |                                               | x                                                 |                                          |

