## 9 Data Management, Statistical Analysis and Record Keeping

## Statistics and Interim Analysis

*The primary research questions for this study are:*

- Does the SMART program, compared with usual care, change health-related quality of life (primary outcome) measured 16-weeks and 12-months following randomisation?

AND

- Does the SMART program, compared with usual care, change peripheral muscle strength, muscle mass, exercise tolerance, exercise adherence and chemotherapy completion rates (secondary outcomes) measured 16 weeks following randomisation?

The analyses for this research question will be performed according to the intention to treat principle. For the primary outcome, health-related quality of life, with 4 assessment points, linear models will be used to account for repeated measures with participant ID entered as a random effect. The primary time point of interest will be the end of the intervention phase. Group, time and group by time will be analysed as fixed effects and the baseline measure will be entered as a covariate to adjust for random baseline differences. Between group difference for the dependent outcome of chemotherapy completion (yes/no) will be analysed using logistic regression. Between group differences for the remaining secondary measures (peripheral muscle force-generating capacity, muscle mass, exercise tolerance) will be examined using linear regression with the corresponding baseline measure used as a covariate. Data transformations or alternative models (such as gamma distribution) will be considered if there is poor model fit.

Missing data will be examined and multiple imputations investigated (assuming they are missing at random). Models will be adjusted for covariates, randomisation variables and confounders such as age. Estimates of the effects will be reported with their corresponding 95% confidence intervals.

*The first secondary research question is:*

- Do factors such as adherence, treatment pathway and cancer stage moderate the magnitude of any change in primary or secondary outcomes? (i.e. moderator analysis)

To understand any moderator effects, the listed covariates will be entered into a multivariable model using the outcomes listed above. In addition, adherence will be examined to see if it mediates the relationship with the outcomes, by calculating the indirect through the use of partial coefficients.

*The second secondary research question is:*

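### Exercise adherence is compared between arms and used as moderator and mediator, but exercise participation is not scheduled for measurement before randomisation

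*Protocol*

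**What the plan says.** Section 3 (Trial Aims / Objectives / Hypotheses), primary research question 2, asks whether the programme changes a set of outcomes including "exercise tolerance, exercise adherence and chemotherapy completion rates (secondary outcomes) measured 16 weeks following randomisation". The first secondary question lists adherence among the possible moderators. The Statistics and Interim Analysis section adds that adherence will be examined as a mediator.

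Section 7, under Other Variables, says how exercise adherence is obtained in both groups: participants "recall the number of minutes spent engaging in moderate or vigorous intensity exercise", with details of any resistance work. The control group reports through monthly calls and diaries, the experimental group through weekly sessions and diaries. All of these contacts follow randomisation.

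In Table 1 (Timing of outcomes), the row "Participation in exercise" is marked only in the weekly intervention-phase column. The baseline assessment described at the start of Section 7 covers questionnaires, strength, six-minute walking distance and body composition, but not exercise participation.

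Under Blinding and Randomisation, factor (iii) records whether the person regularly engaged in "exercise (or not) prior to their BC diagnosis". No amount, type or look-back period is given. Entry is open to an "Adult with newly diagnosed breast cancer (within the last 6 months").

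For muscle force, muscle mass and exercise tolerance, the analysis is "linear regression with the corresponding baseline measure used as a covariate". The models are also to be adjusted for the randomisation variables and for confounders, with age as the example.

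**The concern.** Exercise is the behaviour the programme sets out to change. Eligibility sets no activity limit, and the stated aim is to build up to the target or to maintain it, so people already at the target and people doing nothing can both enter. Without minutes at time zero, the report cannot show who was building up and who was maintaining.

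Two analyses lose something:

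- **The between-arm comparison of exercise at 16 weeks.** It forgoes the precision that a baseline covariate would bring.
- **The moderator and mediation analyses.** These are the more exposed, because adherence is not randomised. Activity at entry plausibly influences both later adherence and later quality of life or fitness, which makes it an obvious confounder. Only a coarse yes/no about the time before diagnosis is available to control it.

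**Working it through.** **Step 1. Which outcomes in primary question 2 have a baseline value?** From Table 1 (Timing of outcomes):

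| Outcome | Pre-randomisation mark | Could it have one? |
|---|---|---|
| Muscle strength (grip, deltoid, biceps, quadriceps) | Yes | Yes |
| Muscle mass | Yes | Yes |
| Exercise tolerance (6MWT) | Yes | Yes |
| Chemotherapy completion | No | No, chemotherapy received against plan accrues over treatment |
| Exercise participation | No | Yes, weekly minutes can be recalled at entry |

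Exercise is the only outcome in that question that could have a baseline value and has none.

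**Step 2. What else recorded before allocation bears on exercise?** There is factor (iii), plus six-minute walking distance, exercise intention, self-efficacy and automaticity. These are related to activity, but none gives minutes of current exercise.

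**Step 3. Does the pre-diagnosis item stand in for current activity?** Entry can be up to 6 months after diagnosis, and the background section reports that "23% reduce their usual activity level during cancer treatment". Habit before diagnosis and activity at entry can therefore differ. The documents do not say how often they do.

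**Step 4. Precision.** The protocol's own sample size is for quality of life and is not in dispute. With difference 8, SD 20.52, two-sided α = 0.05 and power 0.8, n = 2 × 20.52² × (1.960 + 0.842)² / 8² ≈ 103.3, rounded up to 104 per group. Then 104 / 0.8 = 130 recruited per group.

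Taking 104 per group as the evaluable number for the exercise outcome as well, the standardised difference detectable with 80% power and no baseline value is (1.960 + 0.842) × √(2/104) = 0.389 SD. A baseline value correlated r with follow-up leaves a fraction 1 − r² of the variance and multiplies the detectable difference by √(1 − r²). The values of r are assumptions:

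| r (assumed) | Variance removed, r² | Detectable difference |
|---|---|---|
| 0 (no baseline) | 0% | 0.389 SD |
| 0.3 | 9% | 0.389 × √0.91 = 0.371 SD |
| 0.5 | 25% | 0.389 × √0.75 = 0.336 SD |
| 0.6 | 36% | 0.389 × √0.64 = 0.311 SD |

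These gains are relative to no adjustment at all. The plan already adjusts for factor (iii), which should carry part of the same information, so the extra gain is probably smaller.

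**The case against.** The strongest reply is that adherence to a programme has no value before the programme starts, that the analysis section does not list adherence among the baseline-adjusted measures, and that its model may be in an analysis plan not shown. The first part would be decisive if adherence meant attendance. Here it is recalled exercise minutes, collected in both arms, and minutes do have a value at entry. How to model the outcome can wait for the analysis plan, but a baseline value that was never collected cannot be recovered there. It is fair to add that the appended questionnaires are not shown and the descriptive variables are given only as examples. Even so, the timing table has no baseline mark.

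A reader might go further in four ways that the documents do not support:

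- **That high activity at 16 weeks could be prior habit, so the comparison is biased.** Allocation is randomised and concealed, so prior habit falls on both arms by chance. The loss is in precision and interpretation.
- **That stratifying on pre-diagnosis habit is an error because it is out of date.** It is a legitimate prognostic factor, and one that treatment does not disturb. The undefined term is missing detail. Inconsistent classification before concealed allocation weakens balance and adjustment without biasing the comparison.
- **That about a quarter of entrants are misclassified.** The 23% refers to reductions during treatment, not between diagnosis and randomisation. A later decline does not make a label of earlier habit wrong.
- **That factor (iii) should be redefined as meeting the full exercise target.** The background says approximately 80% do not meet the recommendations, which would put about 0.20 × 260 = 52 people in the upper level. With two locations and an assumed two or three treatment pathways, that is 4 or 6 cells averaging 13 or about 9 people. Changing the rule after recruitment has begun would also mix two definitions.

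**Conclusion.** The point holds as a gap in baseline measurement. An outcome compared between arms, and used as moderator and mediator, has no scheduled value before randomisation, and the existing yes/no item is only a partial substitute. The primary endpoint, quality of life at 16 weeks, is unaffected and keeps its own baseline covariate.

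The size is modest and uncertain. For an assumed r of 0.3 to 0.6, 9% to 36% of residual variance in one secondary outcome could be removed relative to no adjustment, with less expected once factor (iii) is in the model. The effect on the moderator and mediation analyses cannot be put in figures from the protocol, but they have the most to gain. This is a worthwhile, inexpensive improvement and not a threat to the trial's main conclusion.

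**What to change.** At the existing baseline visit, before randomisation, ask the recall items the protocol already uses: current weekly minutes of moderate and vigorous exercise, and resistance sessions. Add a pre-randomisation mark to the exercise participation row of Table 1 (Timing of outcomes). State that this value will be the baseline covariate in the between-arm comparison of exercise and a confounder in the adherence moderator and mediation models.

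Keep factor (iii) as pre-diagnosis habit, and analyse it as recorded at randomisation.

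The cost is a few extra questions at a visit of about 90 minutes, plus one table entry. The main downside is that the value will be missing for anyone already randomised (the milestones put the start of recruitment in March 2024). The analysis would need to say how those participants are handled.

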## Intervention/Product Description

The active ingredients of SMART program are described below. These will be delivered in an adaptable way; specific to each individual, periodised according to any treatment symptoms and progressed/regressed accordingly.

### 1) Exercise prescription

The target behaviour of the SMART program is for participants to work towards or maintain 150 minutes per week of moderate intensity aerobic exercise (or 75 minutes per week of vigorous intensity aerobic exercise), as well as two resistance training sessions per week.

Moderate intensity aerobic exercise will be defined as exercise performed at 60 to 75% of their age predicted maximum heart rate. Vigorous intensity aerobic exercise will be defined exercise performed at > 75% of their age predicted maximum heart rate.

Resistance training session will encompass the major muscle groups in 30 minutes of training and will be defined as completion of 3 sets of 8-12 repetitions of strength-based or functional tasks (for example, sit to stand, bicep curls, squats). The goal will be to report an intensity that is perceived a 15 ('hard') on the 6 to 20 Rating of Perceived Exertion. Intensity will be progressed by increasing the resistance and/or to a more challenging movement pattern.

### 2) Weekly sessions with a physiotherapist

Once a week, participants will meet with a physiotherapist, either in person (at RPH) or via telehealth. This session will be approximately one-hour in duration. During this session, (i) the participant and physiotherapist will reflect on the achievement of the goals set towards the target behaviour for the previous week, (ii) the participant will perform a supervised exercise session that comprises aerobic and resistance exercise and the physiotherapist will provide feedback and reassurance and, (iii) the participant and physiotherapist will plan the exercise training sessions for the following week.

Goal setting will be individualised and consider; (i) participant's preferences and, (ii) the timing and severity of the likely or experienced side effects of the BC treatment. Goals will be agreed upon that are Specific, Measurable, Achievable, Relevant and Time-bound (SMART). An example of an exercise plan is included in Table 1 below.

Table 1: Example exercise plan

| My exercise plan for week beginning 03/06/24: |      |                                                                                                                     |
|-----------------------------------------------|------|---------------------------------------------------------------------------------------------------------------------|
| Monday                                        | 2pm  | Gym session 60 mins (20-30 mins aerobic, 30 mins resistance exercises). Refer to your online exercise prescription. |
| Tuesday                                       | 10am | Walk dog for 45 minutes (aim for heart rate of 120bpm)                                                              |
| Wednesday                                     |      | Walk dog for 45 minutes (aim for heart rate of 120bpm)
Chemo in the afternoon                                    |
| Thursday                                      | 10am | Gym session 60 mins (20-30 mins aerobic, 30 mins resistance exercises). Refer to your online exercise prescription. |
| Friday                                        |      | Day of rest                                                                                                         |

|                                                                 |  |                                                                                                                                                                                                            |
|-----------------------------------------------------------------|--|------------------------------------------------------------------------------------------------------------------------------------------------------------------------------------------------------------|
| Saturday                                                        |  | Day of rest                                                                                                                                                                                                |
| Sunday                                                          |  | Day of rest, or consider one of your low intensity programs (30 min light walk aiming for heart rate of 90bpm or your online yoga program), if you are starting to feel better after your chemo this week. |
| *Don't forget to log your exercises on your online diary |  |                                                                                                                                                                                                            |

